Background: The artemisinin resistance is not just on the Thai-Cambodia border, but may have extended to or emerged on the Thai-Myanmar, China-Myanmar and Cambodia-Viet Nam borders, confirmatory artemisinin monotherapy in vivo studies and molecular fingerprinting of parasite genomes to track artemisinin resistance (gene flow) moving around the region is even more important now. Of the data presented from these countries, the slow parasite clearance time (PCT) following treatment with artemisinin derivatives was of greatest concern. With combination therapy, artesunate usually provides the initial rapid decrease of PCT, with 95% of patients clearing peripheral parasitaemia within 48 hours, hence if the PCT is slow despite the drug being in the blood at adequate levels, this could provide evidence that it is failing.

Objective: To assess the efficacy artesunate 4 mg/day over 7 days for the treatment of uncomplicated *Plasmodium falciparum* malaria in Kawthaung (Tanintharyi Division) in Myanmar.

Methods: An antimalarial drug efficacy trial will be conducted in Kawthaung (Tanintharyi Division), Mzanmar. The participants will be febrile people > 18 years with confirmed uncomplicated *P. falciparum* infection. Patients will be treated with artesunate 28 mg/kg over 7 days. Clinical and parasitological parameters will be monitored over a 28-day follow-up period to evaluate drug efficacy. The study will be conducted from October 2010 to September 2010. The results of this study will be used to assist the Ministry of Health of Myanmar in assessing the current national treatment guidelines for uncomplicated *P. falciparum* malaria and mapping the extent of artesunate resistance.

1. Background

The current national treatment guideline for the treatment of uncomplicated malaria is artemether-lumefantrne, dihydroartemisinin-piperaquine and artesunate-mefloquine. An antimalarial drug efficacy trial was conducted in 4 sentinel sites (Kayin, Mon, Kachin and Yakhine States) in Myanmar between June and November, 2007. Patients were treated with artesunate-amodiaquine combination and artemether-lumefantrine combination. A total of 535 subjects (171 subjects in Yakhine, 71 subjects in Kayin, 151 subjects in Kachin, and 142 subjects in Mon state) were enrolled for therapeutic efficacy study. 296 subjects were treated with artemether-lumefantrine and 239 subjects with artesunate-amodiaquine after random selection. In in artesunate-amodiaquine group there was one late parasite failure case each in Kachin, Kayin and Mon State. In artemether-lumefantrine group there was one late parasite failure (LPF) at day 14 in Kayin State, 2 late treatment failure cases each in Mon state and Yakhine State. The late treatment failure cases were compared with genotypic profiles of the pre- and post parasite strains by the malaria parasite genes, msp1, msp2 and glurp. After molecular analysis, one patient from Kachin was re-infected case and the other two (Kayin & Mon) were true recrudescence in artesunate-amodiaquine group, and those from Yakine are re-infected cases and 1 from Kayin, 2 from Mon State were true recrudescence to artemether-lumefantrine combination. In a 2008 clinical trial of 3-day artemisinin-piperaquine (Artequick™) at the Defense Services General Hospital, delayed parasite clearance time of >100 hours in 7/50 patients and >90 hours in 2 patients was also observed.

Recently, longer parasite clearance and decreasing efficacy of ACTs were observed in Shwe Kyin and Kawthaung, on the south eastern tip of Myanmar bordering with Ranong, Thailand. A total of 168 cases were completed for study in artemether-lumefantrine group and 153 in dihydroartemisinin-piperaquine group. There was one ETF case at Shwe Kyin, who had persistence of parasitemia up to day 3 with parasite count more than 10% of the day 0 count. Clinically 8 recurrence cases in artemether-lumefantrine group and 4 cases in dihydroartemisinin-piperaquine group were noted, but reinfection can be excluded after molecular analysis. The persistant of parasitaemia was noted in all study sites for both combinations and marked elevation was noted in patients treated with dihydroartemisinin-piperaquine at Kawthaung (18.5%). This same site in Thailand has been showing increasing artesunate-mefloquine failures since 2006. The presented results of that therapeutic efficacy trials in Cambodia and Thailand were the failure rates of combinations with artemisinin derivatives and mefloquine and artemether-lumefantrine in both countries, as well as increased parasite clearance time (PCT) from clinical trials using artesuante-mefloquine and artesunate+pyronaridine in Cambodia. Of the data presented from the two countries, the slow PCT following treatment with artemisinin derivatives was of greatest concern. With combination therapy, artesunate usually provides the initial rapid decrease of PCT, with 95% of patients clearing peripheral parasitaemia within 48 hours, hence if the PCT is slow despite the drug being in the blood at adequate levels, this could provide evidence that it is failing. The resistance monitoring shows the proportion of patients who are parasitaemic on day 3 is the best measure of slow parasite clearance from available clinical trial data and should be used as an early warning system for development of artemisinin resistance.

The critical question is whether artemisinin derivatives are actually failing or not against current recommended total dosage (12 mg/kg) or higher dosage. Since artemisinin resistance is not just limited to the Thai-Cambodia border, but may have extended to or emerged on the Thai-Myanmar, China-Myanmar and Cambodia-Viet Nam borders, confirmatory artemisinin resistance through monotherapy in vivo studies and molecular fingerprinting of parasite genomes to track artemisinin resistance (gene flow) moving around the region is even more important now.

The trial described here proposes to assess the PCT and the efficacy after 4mg/kg oral artesunate over 7 days. The results of this study will be compared to recent data from patients in Cambodia and Thailand treated with equivalent doses of artemisinin derivatives.

2. Objectives

The primary objective of this study is to assess the PCT and efficacy of artesunate 4mg/kg/day in the treatment of uncomplicated *P. falciparum* malaria in Kawthaung (Tanintharyi Division) in Myanmar.

The specific objectives are:

- to measure the PCT with blood sampling for parasite counts twelve hourly and to measure clinical and parasitological efficacy of artesunate 4mg/kg/day over 7 days in patients aged > 18 years, suffering from uncomplicated falciparum malaria
- to determine the proportion with early treatment failures, late clinical failures, late parasitological failures or adequate clinical and parasitological response as indicators of efficacy
- to differentiate recrudescence from new infection by polymerase chain reaction (PCR) analysis
- to evaluate the number of adverse events
- to formulate recommendations and to enable the Ministry of Health to make informed decisions about whether the current national antimalarial treatment guidelines should be updated. The results of this study will indicate if artemisinin resistance is present in Myanmar which allows a better mapping of the situation of artemisinin resistance in the region and indicate if containment effort should be started.

The secondary objectives are:

- to determine the polymorphism of molecular markers for antimalarial resistance; and
- to determine the blood concentration of artesunate and dihydroartemisinin

3. Methods

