3.1 Study design

People with uncomplicated malaria presenting at the Kamaukkyi 38 mile station hospital who meet the study inclusion criteria will be enrolled and treated on site with artesunate 4mg/kg/day until PCT and monitored for 28 days. The follow-up will consist of a fixed schedule of check-up visits and corresponding clinical and laboratory examinations. On the basis of the results of these assessments, the patients will be classified as having therapeutic failure (early or late) or an adequate response. The proportion of patients experiencing therapeutic failure during the follow-up period will be used to estimate the efficacy of the study drug(s). PCR analysis will be used to distinguish between a true recrudescence due to treatment failure and episodes of reinfection.

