4.3 Rescue treatment

If a patient meets one of the criteria for therapeutic failure, ETF and LTF cases, he/she will receive the other artemether-lumefantrine. If the patient is reinfected with another malaria species (*P. vivax, P. malariae or P. ovale*) he/she will receive chloroquine total dose of 25mg base/kg over three days, followed by primaquine 0.25mg/kg/day for 14 days (except for *P. malariae*) according to the current national recommendations.

If the patient vomits the treatment twice, he/she will receive parenteral therapy with artemether IM (80mg/ amp) injection 160mg at 0hrs and l2th hours, and 80 mg at 24th and 48th hours (total = 480mg) plus oral mefloquine (500mg) x 2 doses at 48th and 54th hours and be withdrawn from the study.

With any sign of severe malaria, the study patient will be treated with quinine injection 8 mg/kg of quinine base every 8 hours. Quinine will be given 3 time a day until the patient can reliably take oral medication. The patient will then continue on oral quinine (3x8 mg/kg/day) until they have completed seven days treatment. A seven days course of doxycycline (3 mg/kg/day) will be given also to patients as well as relevant supportive treatments.

5. Evaluation criteria

The study end-point is the classification assigned to a patient. Valid study end-points include: the number of patients parasite positive at day 3, PCT, parasite reduction rate (slope of the log-linear parasite clearance curve), the parasite reduction rate at 48 hours, treatment failure, completion of the follow-up period without treatment failure, loss to follow-up, withdrawal from study, and protocol violation. At all times, the well-being of the patient will take priority over his or her continuation in the study. Secondary end-point is the pharmacokinetic profile of the patients.

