8.1 Sample size

The estimated prevalence of patients positive at day 3 after artesunate 4 mg/kg/day over 7 day in the area is 15%. At a confidence level of 95% and a precision around the estimate of 10%, a minimum of 40 must be included. With a 20% increase to allow loss to follow-up and withdrawals during the 28-day follow-up period, a number of 50 patients should be targetted in the study per site.

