8.2 Analysis of data

WHO excel programme and SPSS programme will be used for data management and analysis. Data will be analysed by two methods: the Kaplan-Meier method and per-protocol analysis. In addition to the reasons for withdrawal listed in section 3.8, patients will be considered withdrawn from the analysis if the PCR results are unclassifiable or if the results of PCR indicate that the failure is due to reinfection with *P. falciparum* or *P. vivax.*

The final analysis will include:

- a description of all patients screened and the distribution of reasons for non-inclusion in the study;
- a description of all the patients included in the study;
- the number of adverse events and serious adverse events in all the patients included in the study;
- the proportion of patients lost to follow-up or withdrawn, with 95% confidence intervals and a list of reasons for withdrawal;
- the cumulative incidence of success and failure rates at day 28, PCR-uncorrected and PCR-corrected; and
- the proportion of early treatment failure, late clinical failure, late parasitological failure and adequate clinical and parasitological response at day 28, with 95% confidence intervals, PCR-uncorrected and PCR-corrected.
- The PCT, parasite reduction rate (slope of the log-linear parasite clearance curve), the parasite reduction rate at 48 hours, and the number of patients parasite positive at day 3;
- The pharmacokinetic profile of the patients.

Guidelines on calculating the cumulative success or failure rate, the proportion of adequate clinical and parasitological response and treatment failure are given in Appendix 9.

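### The primary objective names PCT and efficacy, the sample size rests on day-3 positivity, and no measure is ranked or tied to the promised resistance and containment statement

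*Protocol*

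**What the plan says.** Section 2 of the protocol sets two outcomes side by side: "The primary objective of this study is to assess the PCT and efficacy of artesunate 4mg/kg/day". Section 3.1 then defines how efficacy is measured: "The proportion of patients experiencing therapeutic failure during the follow-up period will be used to estimate the efficacy".

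Section 8.1 uses neither PCT nor 28-day failure. It starts from "The estimated prevalence of patients positive at day 3 after artesunate 4 mg/kg/day over 7 day in the area is 15" per cent, asks for 95% confidence and a precision of 10%, and arrives at a minimum of 40 patients and a target of 50. No objective in section 2 mentions day-3 positivity, although section 1 says that "the proportion of patients who are parasitaemic on day 3 is the best measure of slow parasite clearance from available clinical trial data".

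Section 5 gives a list: "Valid study end-points include: the number of patients parasite positive at day 3, PCT, parasite reduction rate (slope of the log-linear parasite clearance curve"), followed by the 48-hour reduction, treatment failure, completion without failure, and then loss to follow-up, withdrawal and protocol violation. Only the pharmacokinetic profile is given a rank, as secondary.

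Section 8.2 says "Data will be analysed by two methods: the Kaplan-Meier method and per-protocol analysis". Day-28 outcomes are to be shown PCR-uncorrected and PCR-corrected, and the outcome proportions carry 95% confidence intervals. Day-3 positivity appears only as a number of patients, with no interval.

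Section 2 also commits the results to a conclusion: "The results of this study will indicate if artemisinin resistance is present in Myanmar", and they are to "indicate if containment effort should be started". Section 5.1.1 calls the study descriptive.

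**The concern.** Choosing the primary endpoint is a protocol decision, and this protocol settles it in two ways that do not match. The objective points to PCT and efficacy, and the only precision statement covers day-3 positivity. The resistance and containment statement has no endpoint attached to it. If slow clearance and good 28-day efficacy appear together, the protocol does not say which of them carries the conclusion, so the weight given to each can be settled after the results are known.

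A second problem follows for the sized endpoint. Section 8.2 withdraws patients from the analysis when PCR is unclassifiable or shows reinfection, and sections 3.7 and 3.8 censor or exclude those lost or withdrawn. None of these rules is limited to the day-28 outcome. Read literally, they could remove a patient whose day-3 film is already known because of something that happened on day 14 or day 21.

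**Working it through.** **1. The stated sample size.** Inputs from section 8.1: p = 0.15, d = 0.10, z = 1.96.

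- n = z² p(1 − p)/d² = 3.8416 × 0.1275/0.01 = 48.98, so 49 evaluable patients. The stated 40 is not reproduced.
- At 90% confidence the formula gives 34.5, so 35. A finite-population correction reaches 40 only for a population of roughly 200 to 218, and the protocol states none.
- The second step does reproduce: 40/(1 − 0.20) = 50.
- Half-width at n = 40: 1.96 × √(0.1275/40) = 0.111, or ±11.1 points. At n = 50 with no losses it is ±9.9 points.
- With 49 evaluable patients and the same 20% allowance: 49/0.80 = 61.25, so 62 enrolled.

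For PCT and for 28-day failure no sample size can be computed, because the protocol gives no SD, expected rate or margin for either.

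**2. Can clearance and efficacy disagree under the protocol's own definitions?** Appendix 4 counts day-3 parasitaemia as early failure only with a temperature of at least 37.5 °C, with a density of at least 25% of day 0, or with danger signs or severe malaria. A day-2 count above day 0 is a separate criterion. Entry densities run from 10,000 to 100,000/µl (section 3.5), so the 25% line lies between 2,500 and 25,000/µl. An afebrile patient below that line on day 3, with no other failure criterion, who is clear from day 7 through day 28 is an adequate response.

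A hypothetical result with 50 patients shows the effect, if 8 are of this kind and nobody fails:

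| Measure | Estimate | Exact 95% CI |
|---|---|---|
| Day-3 positivity | 8/50 = 16% | 7.2 to 29.1% |
| 28-day failure | 0/50 = 0% | 0 to 7.1% |

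The reverse is also possible: a patient who clears early and recrudesces before day 28 is negative on day 3 and a late failure.

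**3. Can PCT and day-3 positivity disagree?** Sections 5.2.4 and 6.2 call for 12-hourly films until clearance. Leaving aside films that turn negative and then positive again, a patient positive at 72 h has not cleared by 48 h. Section 1 gives the quantified norm: 95% cleared within 48 hours. If 15% are positive at 72 h, at most 85% have cleared by 48 h, so that norm is missed by at least 10 points and both measures signal. The converse does not hold: a patient who clears at 60 h is late against 48 h but negative on day 3.

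**4. The background data, as illustration only.** Section 1 reports 18.5% persistent parasitaemia with dihydroartemisinin-piperaquine at Kawthaung, and 4 recurrences among 153 patients in that group: 4/153 = 2.6%, exact 95% CI 0.7 to 6.6%. The Kawthaung denominator is not given. The smallest one that fits 18.5% is 27 (5/27). If all four recurrences were there, the site rate would be 4/27 = 14.8%. With 54 patients (10/54) it would be at most 4/54 = 7.4%.

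**The case against.** The study is descriptive, and section 8.2 requires PCT, slope, 48-hour reduction, day-3 positivity and all the day-28 rates to be reported. Appendix 9 fixes how each patient counts in the day-28 analyses. Nothing listed can therefore be quietly dropped. That stands, and it limits the harm. It does not say which result drives a yes/no statement on resistance.

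Day-3 positivity is also, in effect, PCT cut at 72 h, so section 8.1 sizes a dichotomy of one of the named outcomes. That stands too. On the clearance side the mismatch is mostly one of naming, and the real divergence is between clearance and 28-day efficacy.

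Four stronger readings are tempting but not supported:

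- A reader might infer that a normal median PCT could contradict 15% day-3 positivity. The protocol sets no norm for the median, and against its 95% norm the two agree, as shown above.
- A reader might infer an inflated false-positive rate from several unranked measures. The protocol has no hypothesis test and no alpha, so there is no error rate to inflate.
- A reader might take 18.5% against 2.6% as proof of divergence. One figure is a single site and the other is pooled. The 18.5% is not labelled day 3. Both come from a combination whose partner drug can cure despite slow clearance. Section 1 itself reports longer clearance and falling efficacy together.
- A reader might conclude that the resistance statement should rest on day-3 positivity alone. Section 1 treats slow clearance as evidence only when drug levels are adequate, which is why concentrations are measured, and it gives day-3 positivity an early-warning role.

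**Conclusion.** The point holds as an inconsistency that should be corrected. The named primary objective and the sized endpoint differ, the efficacy measures are unranked, and the resistance and containment statement has no stated basis. The possibility that clearance and 28-day efficacy disagree follows from Appendix 4 and needs no outside assumption. How often it would happen with artesunate alone cannot be derived from the protocol.

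The size that can be stated is modest. The sized endpoint needs 49 evaluable patients rather than 40, and 40 gives ±11.1 points rather than ±10. These figures assume the usual normal approximation and an absolute precision of 10 points. The possible loss of patients with a known day-3 film rests on a literal reading of sections 3.7, 3.8 and 8.2, which do not say whether their exclusions apply to day-3 positivity.

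**What to change.** - **Sections 2 and 5:** name the proportion with asexual parasitaemia at day 3 (72 h) as the primary clearance endpoint. Section 8.1 already sizes it, and section 1 already prefers it as a measure of slow clearance.
- **Section 8.2:** report it with a 95% CI in all treated patients who have a day-3 film, whatever happens to them later. State that the PCR, loss and withdrawal rules apply to the day-28 outcome only.
- **Ranking:** label PCT, slope and 48-hour reduction as supporting clearance measures, and PCR-corrected Kaplan-Meier failure at day 28 as the key efficacy endpoint.
- **Resistance statement:** say in advance that it rests first on the day-3 estimate, read together with the supporting clearance measures, drug concentrations and day-28 failure.
- **Section 8.1:** restate the precision. Either plan for 49 evaluable patients or keep 40 and state about ±11 points.

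The cost is mostly wording, with no new visits or assays. Patients are in hospital for the first 7 days, so few day-3 films should be missing. A target of 50 yields 49 evaluable if at most one film is missing, whereas keeping the 20% allowance means 62 enrolled. The downside is that a signal seen only in a supporting measure will carry less weight.

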3.1 Study design

People with uncomplicated malaria presenting at the Kamaukkyi 38 mile station hospital who meet the study inclusion criteria will be enrolled and treated on site with artesunate 4mg/kg/day until PCT and monitored for 28 days. The follow-up will consist of a fixed schedule of check-up visits and corresponding clinical and laboratory examinations. On the basis of the results of these assessments, the patients will be classified as having therapeutic failure (early or late) or an adequate response. The proportion of patients experiencing therapeutic failure during the follow-up period will be used to estimate the efficacy of the study drug(s). PCR analysis will be used to distinguish between a true recrudescence due to treatment failure and episodes of reinfection.

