3.3 Study population

The population will consist of patients with uncomplicated *P. falciparum* malaria attending the study health clinic who are aged > 18 years. All adult patients will sign an informed consent form for participation. Patients will be hospitalized for the 7 first days.

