4.1 Antimalarial treatment

The patients will be received artesunate 50 mg per tablet (Guilin Pharmaceutical Company, PRC) 4mg/kg/day for 7 days. Each dose administration will be observed and recorded. The correct drug dosage will be determined from the dosing chart (Appendix 3).

All doses of medicine will be administered under the supervision of a qualified member of the staff designated by the principal investigator. The study patients will be observed for 30 min after medicine administration for adverse reactions or vomiting. Any patient who vomits during this observation period will be re-treated with the same dose of medicine and observed for an additional 30 min. If the patient vomits again, he or she will be withdrawn and offered rescue therapy.

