Appendix 6. Schedule of follow-up activities

|  | Day | | | | | | | | | |
| --- | --- | --- | --- | --- | --- | --- | --- | --- | --- | --- |
| 0 | 1 | 2 | 3 | 7 | 14 | 21 | 28 | Any other |  |
| **Procedure** |  |  |  |  |  |  |  |  |  |  |
| Clinical assessment | X | X | X | X | X | X | X | X | (X) |  |
| Temperature | X | X | X | X | X | X | X | X | (X) |  |
| Blood slide for parasite count | X |  | X | X | X | X | X | X | (X) |  |
| Urine sample | (X) |  |  |  |  |  |  |  |  |  |
| Blood for:  genotyping  molecular markers  antimalarial blood concentration | X  X  11 X | X |  |  | X | X | X | X | X |  |
| Treatment |  |  |  |  |  |  |  |  |  |  |
| Medicine to be tested from day 0 to day 6 included | X | X | X | X |  |  |  |  |  |  |
| Rescue treatment |  | (X) | (X) | (X) | (X) | (X) | (X) | (X) | (X) |  |

Parentheses denote conditional or optional activities. For example, treatment would be given on days 1 and 2 only for 3-day dosing. On day 1, the patient should be examined for parasitaemia if he or she has any danger signs. Rescue treatment could be given on any day, provided that the patient meets the criteria for treatment failure. Extra days are any days other than regularly scheduled follow-up days when the patient returns to the facility because of recurrence of symptoms. On extra days, blood slides may be taken routinely or at the request of the clinical staff.

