**Day 2, Day 3**

- clinical assessment; referral in cases of severe malaria or danger signs;
- measurement of axillary temperature;
- parasitological assessment;
- treatment, third to seventh dose (until day 6) or alternative treatment in case of early treatment failure.

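### Section 3.1 ends artesunate at parasite clearance, while every other section that gives a duration fixes a 7-day course; a minor inconsistency to correct in 3.1

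*Protocol*

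**What the plan says.** Section 3.1 (Study design) has patients "treated on site with artesunate 4mg/kg/day until PCT and monitored for 28 days". PCT is the protocol's abbreviation for parasite clearance time, so the sentence ties the end of dosing to each patient's own clearance.

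The other places that give a duration for the study drug say 7 days:

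- Synopsis, Methods: "Patients will be treated with artesunate 28 mg/kg over 7 days". This is the only place where the 28 mg/kg total is printed.
- Section 1, closing paragraph: 4 mg/kg over 7 days.
- Section 2, first specific objective: "to measure clinical and parasitological efficacy of artesunate 4mg/kg/day over 7 days".
- Section 4.1: "4mg/kg/day for 7 days".
- Section 8.1: the assumed day-3 prevalence is stated for the 7-day regimen.
- Appendix 6, table row label: "Medicine to be tested from day 0 to day 6 included".
- Appendix 6, list for days 2 and 3: "treatment, third to seventh dose (until day 6").

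Section 3.3 adds "Patients will be hospitalized for the 7 first days", and section 3.2 repeats the 7-day hospital stay. In sections 5.2.4 and 6.2, clearance is the stopping rule for something else: the 12-hourly blood films.

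**The concern.** A protocol should give one duration for its only study drug. Section 3.1 gives one that depends on response, and the rest of the document gives one that does not.

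If 3.1 were followed, faster clearers would receive less drug. The efficacy part of the primary objective is measured by failure rates at day 28, PCR-uncorrected and PCR-corrected (section 8.2 and Appendix 9). Those rates would then come from a mixture of short courses and would not describe the 7-day regimen named in the specific objective. Section 1 asks whether artemisinins fail at the recommended total of 12 mg/kg or at a higher dose. A patient who stopped at a 48-hour clearance would receive no more than 12 mg/kg, so the higher dose would go untested in that patient.

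The paperwork gives the later doses little visibility. The Appendix 6 table marks treatment only under days 0 to 3 and has no columns for days 4 to 6. Its note uses a 3-day regimen as an example. The case report forms run from day 3 to day 7, with only the form for any other day in between. The doses that 3.1 would drop are therefore the ones least prompted by the forms.

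**Working it through.** **Step 1. Reproduce the stated total.** Inputs: 4 mg/kg once daily (section 4.1, Appendix 3) and day 0 to day 6, which is 7 doses (Appendix 6). Total = 4 × 7 = 28 mg/kg, which matches the synopsis. This is a nominal figure. Rounding to quarter tablets in Appendix 3 gives 3.85 mg/kg/day (150 mg at 39 kg) to 4.17 mg/kg/day (125 mg at 30 kg), or about 26.9 to 29.2 mg/kg over 7 days.

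**Step 2. Can 3.1 be read so that the conflict disappears?** One could take its clearance clause as the length of the stay on site and not of treatment. That reading conflicts with the 7-day hospital stay in sections 3.2 and 3.3, so it only moves the inconsistency elsewhere.

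**Step 3. Dose received if 3.1 were followed.** Assumptions: doses are due at 0, 24, 48, 72, 96, 120 and 144 h; films are read every 12 h; dosing stops at the first negative film, time T. The protocol does not say what happens to a dose due exactly at T, so both possibilities are shown. Dose = 4 mg/kg × number of doses due before T (dose at T withheld) or up to and including T (dose at T given).

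| First negative film, T | Dose at T withheld | Dose at T given |
|---|---|---|
| 48 h | 2 doses, 8 mg/kg, 8/28 = 29% | 3 doses, 12 mg/kg, 12/28 = 43% |
| 84 h (earliest if still positive at 72 h) | 4 doses, 16 mg/kg, 57% | 4 doses, 16 mg/kg, 57% |
| 144 h | 6 doses, 24 mg/kg, 86% | 7 doses, 28 mg/kg, 100% |
| 156 h | 7 doses, 28 mg/kg, 100% | 7 doses, 28 mg/kg, 100% |

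The 48-hour row matters most, because section 5.1.1 expects clearance usually within that time. The shortfall there is 28 − 12 = 16 to 28 − 8 = 20 mg/kg, far larger than the tablet-rounding variation in step 1. Anyone first negative before 144 h would get less than the full course under either convention.

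**Step 4. Which results would change?** Clearance time and slope use counts up to clearance, before a stopping rule at clearance could act. The 48-hour reduction and day-3 positivity are settled early and depend mainly on patients still under treatment. Section 8.1 sizes the trial on day-3 positivity. These are essentially unaffected. Only the day-28 outcomes depend materially on doses given after clearance.

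**The case against.** The best answer is that the protocol already settles the matter. Section 3.1 is a short design summary. Section 4.1 is the treatment section and says 7 days, the Appendix 6 text counts doses to the seventh, and every dose is observed and recorded during a 7-day admission. Sections 3.8 and 9.4 speak of completing a full course or full dose, which presupposes a fixed length. Nothing sets out how dosing would stop at clearance: there is no rule for the dose due at the clearing film and no discharge rule. On this view a phrase belonging to the blood films has been attached to the drug, and the dose figures describe something unlikely to happen.

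Most of this stands. It rules out a stronger reading that a reader might infer: that the protocol contains two competing regimens, or that 3.1 is the operative dosing rule. The documents do not support that, because 4.1 and the Appendix 6 text govern dosing and are clear. Nor does the 3-day example in the Appendix 6 note create a third regimen. It is generic template wording under a row that itself says day 0 to day 6.

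What does not fall away is that 3.1 is current text in the Methods, states a dosing duration, and is wrong as written. The treatment marks in the Appendix 6 table do not correct it.

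**Conclusion.** There is an internal inconsistency: 3.1 is wrong as written, and the intended course is evidently 7 days. Severity is minor.

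The size is conditional. Only if staff followed 3.1 over 4.1, with once-daily dosing stopped at the first negative 12-hourly film, would a patient negative at 48 h receive 29% to 43% of the course and the day-28 rates cease to describe the 7-day regimen. The documents give no reason to expect this to be common, and no figure from which a change in the recrudescence rate could be calculated, so none is claimed.

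A reader might also infer that the resistance measures or the sample size are compromised. They are not, for the reasons in step 4 of the working. Nor is 28 mg/kg repeated across the protocol: it is printed once, in the synopsis, and elsewhere follows from 4 mg/kg/day for 7 days.

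**What to change.** In section 3.1, replace the words that end dosing at PCT with: for 7 days (day 0 to day 6, total 28 mg/kg). Keep clearance as the stopping rule only for the 12-hourly blood films in sections 5.2.4 and 6.2.

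In Appendix 6, mark the day 4, 5 and 6 doses in the table and delete the 3-day dosing example from the note.

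The cost is one phrase in 3.1 and a small edit to one table and its note, made through the amendment route in section 8.4 if the protocol has already been accepted. Sample size, visits and drug supply do not change.
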